### Interventions and data collection

From postoperative day 1 to day 7, groups A and B (34 subjects each) will receive 5% hydrogen gas and air, respectively, via nasal cannula for at least 1 h per time and three times per day, totaling 8 h or less (Fig. 1). The study schedule is summarized in Table 1. Upon patient enrollment, the study site staff will make every reasonable effort to follow the participant to ensure that a complete data set is obtained and to avoid associated complexities across the entire study period. All randomized participants who prematurely discontinue study gas inhalation will be considered to be out of the study and will follow the same schedule of events as those participants who continue study gas inhalation, except that the QoR40 and urinary 8-OHdG will not be assessed. All of these participants will be followed until discharge from the hospital as scheduled.
QoR40 scores: Subjects will fill out themselves the previously distributed questionnaire preoperatively, on postoperative days 3 and 7, and at discharge. The questionnaire will be collected by the attending nurse. The primary endpoint is the QoR40 on postoperative day 3.Grade of postoperative complications (Clavien-Dindo score): The attending physician will evaluate on the day of discharge [12].Level of pain (Numerical Rating Scale (NRS)): The attending nurse will record it in the medical record on postoperative days 1, 3, 5, and 7 and on the day of discharge.Amount of dietary intake: The attending nurse will record it in the medical record preoperatively, on postoperative days 3, 5, and 7 and on the day of discharge.Number of pedometer-assessed steps: The number of steps per day will be measured using a pedometer preoperatively and on postoperative days 3, 5, and 7. The attending nurse will record the numbers in the medical record.Inflammatory response (white blood cell count, differential white blood count, and lymphocyte count): They will be measured preoperatively, on postoperative days 0, 1, 3, 5, and 7 and on the day of discharge. They will be automatically recorded in the medical record.Liver function (T-BIL, AST, ALT, ALP, albumin, PT, and ICG): The ICG test will be performed only one time, namely preoperatively. Other measurements will be made preoperatively and on postoperative days 0, 1, 3, 5, and 7 and on the day of discharge. All measurements will be automatically recorded in the medical record.Reactive oxygen level (urinary 8-OHdG level): A subinvestigator will measure preoperatively, on postoperative days 3 and 7 and on the day of discharge and then will record the measurements in the case report form.Adverse events: Common Terminology Criteria for Adverse Events (CTCAE) version 5.0.Duration of study gas inhalation (measured per 24 h and totaled by week)

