#### Primary endpoint

The postoperative recovery level (QoR40) on postoperative day 3 will be evaluated to examine the effectiveness of the hydrogen gas inhalation treatment. The QoR40 will be measured using a questionnaire on postoperative QOL which will be distributed preoperatively. Each patient will independently fill out the questionnaire himself/herself. The scores will be totaled (perfect score: 200 points), and the resulting number will be evaluated as the patient satisfaction level and recovery level. The questionnaire survey will be conducted at 10 AM on postoperative day 3.

The results of previous reports infer that hydrogen gas inhalation has wide effects on many aspects, such as on inflammation and liver function, by inhibiting ROS. The primary endpoint, therefore, is established as the QoR40 on postoperative day 3. A subinvestigator will record the results of the questionnaire in the case report form after the patient is discharged.

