### Safety evaluation

No clinical trial has previously reported any side effects of hydrogen gas inhalation. In this trial, however, the administration of study gas will be immediately discontinued if any serious adverse event occurs.

All adverse events will be recorded and serious adverse events will be totaled separately. If adverse events occur after study gas administration, they will be totaled separately for group A and group B. In addition, the number of patients who experienced the adverse event, number of adverse event episodes, and incidence of adverse events will be determined, and a comparison will be made between groups A and B. All adverse events will be examined regardless of the causal relationship.

Descriptive statistics will be used for clinical test results for each of groups A and B, and clinically significant changes will be totaled. For other parameters, descriptive statistical values will be calculated by group according to the variable type (continuous or categorical variable), or frequencies will be totaled.

A Data and Safety Monitoring Committee (DSMC) will be established independently from the investigator and sponsor. The DSMC comprises an academic pharmacologist, hepatologist, and hepatobiliary surgeon, and the members will review the unblinded study data or whenever an adverse event is reported. The DSMC will advise on continuing or stopping the study based on safety and efficacy considerations.

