### Statistical analysis

For the primary analysis, an unpaired *t*-test with common variance (PPS analysis) will be performed to compare the mean of the QoR40 on postoperative day 3 between groups. The subject population to be analyzed will consist of patients who will have consented to trial participation; who will have been administered, according to schedule, at least the minimum dose of their respective gas for at least 2 days; and whose QoR40 on postoperative day 3 will have been measured. The daily minimum dose will be converted to the duration of administration (3-h duration per day) and will be administered in at least 6 h to less than 7 h. In the sensitivity analysis, a *t*-test will be used on the per-protocol population and similarly on a population which includes patients who received insufficient gas. Content with a focus on the non-unique content will be noted in a statistical analysis plan. No compensation for missing data will be made. The statistical significance level will be set at 5% (two-sided) with a confidence interval of 95% (two-sided). No interim analysis will be performed.

For other items, the effects of hydrogen inhalation will be examined by parameters, such as the extent of hepatectomy (segmentectomy or more extensive resection vs subsegmentectomy or less extensive resection) and hepatic ischemia time (30 min or more vs less than 30 min). In addition, comprehensive and exploratory examinations will be performed, including a comparison of patients with high QoR40 scores and patient characteristics.

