### Analysis of efficacy

The measure of the efficacy of the primary endpoint is the improvement of the QoR40 of the per-protocol population on postoperative day 3. The primary subject population for analysis will be the per-protocol population, but analysis of the intention-to-treat population will also be performed to evaluate the potential for practical application.

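### Day-3 QoR40 is by rule not collected from patients who stop the gas early, so the promised intention-to-treat analysis shrinks to patients still on gas

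*Protocol article*

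**What the plan says.** Four parts of the protocol article bear on this.

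- **Interventions and data collection.** Gas runs from postoperative day 1 to day 7. "All randomized participants who prematurely discontinue study gas inhalation will be considered to be out of the study". They nevertheless follow the same schedule as everyone else, "except that the QoR40 and urinary 8-OHdG will not be assessed". The paragraph ends: "All of these participants will be followed until discharge from the hospital as scheduled". It also asks site staff to "make every reasonable effort to follow the participant to ensure that a complete data set is obtained".
- **Primary endpoint.** "The questionnaire survey will be conducted at 10 AM on postoperative day 3".
- **Statistical analysis and Analysis of efficacy.** The primary t-test uses a per-protocol population that needs at least two days at the minimum dose and a measured day-3 QoR40. A second t-test adds patients who received insufficient gas. Beyond that, "analysis of the intention-to-treat population will also be performed to evaluate the potential for practical application". On missing values: "No compensation for missing data will be made".
- **Safety evaluation.** "the administration of study gas will be immediately discontinued if any serious adverse event occurs".

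**The concern.** An intention-to-treat comparison needs the outcome of every randomised patient, whatever treatment was received. Here the protocol orders that the primary outcome not be taken from some of them, although they remain inpatients and all their other assessments continue. No analysis plan can restore a score that was never collected.

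The loss is also unlikely to be random. A serious adverse event in the first days stops the gas, and such an event plausibly goes with poor recovery, which is what QoR40 measures. If more of these patients stop in one arm, that arm's observed mean rises relative to the other. The intention-to-treat analysis, which should check the per-protocol result, loses the same patients.

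**Working it through.** **1. Who loses what.** The timing rules, set side by side, give four cases.

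| Patient | Day-3 QoR40 | Per-protocol primary analysis | Intention-to-treat analysis |
|---|---|---|---|
| Stops before two days at minimum dose and before 10 AM on day 3 | Not collected | Excluded anyway by the dose condition | Lost through the collection rule |
| Completes two days at minimum dose, then stops before 10 AM on day 3 | Not collected | Lost only through the collection rule | Lost through the collection rule |
| Stops after 10 AM on day 3 | Collected | Unaffected by the rule | Kept; day-7 and discharge QoR40 lost |
| Under-dosed but does not discontinue | Collected | Excluded by the dose condition | Kept |

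The insufficient-gas analysis keeps the last group. It loses patients who are short of gas because they stopped before the day-3 assessment.

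**2. The plan's own figures.** Sample size estimation gives means of 151 and 137 (difference 14), a spread of 30, two-sided alpha 0.20 and power 70%. Reading the 30 as a standard deviation (the article calls it a variance), the two-sample t-test has power 0.697 at 30 per group and 0.707 at 31, so the stated 31 per group reproduces. The allowance of about 10% for dropout is 68 − 62 = 6 patients.

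**3. Bias under assumed stopping.** No stopping rate by arm is given, so these inputs are assumptions. In each arm 20% recover poorly and score *g* points lower. A fraction *e* of the arm stops before the day-3 assessment, all from that subgroup. There is no true difference. Among those still observed, the poor-recovery share is (0.20 − e)/(1 − e), so the spurious difference in favour of the arm with more stopping (A) is

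g × [(0.20 − e_B)/(1 − e_B) − (0.20 − e_A)/(1 − e_A)].

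For 15% vs 5%: 0.15/0.95 − 0.05/0.85 = 0.1579 − 0.0588 = 0.0991. For 20% vs 5%: 0.1579 − 0 = 0.1579.

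| Stopping, A vs B | g = 20 | g = 30 | g = 40 |
|---|---|---|---|
| Equal | 0 | 0 | 0 |
| 15% vs 5% | 1.98 | 2.97 | 3.96 |
| 20% vs 5% | 3.16 | 4.74 | 6.32 |

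The case of 2.97 points is 2.97/14 = 21% of the planned difference.

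**4. Cross-check by counts.** If k of 34 patients in an arm lack a score and would have scored D below the rest, the observed mean is too high by kD/34. With 6 losses in one arm and 1 in the other (7 of 68, about the planned 10%), the spurious difference is 5 × 20/34 = 2.9 points at D = 20 and 5 × 40/34 = 5.9 at D = 40. With SD 30 and no true effect, the two-sided 5% t-test then rejects in about 7% and 12% of trials.

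**5. Without assuming who is missing.** If items score from 1 to 5 (the minimum of 1 is an assumption), totals run from 40 to 200. Three missing of 34 leave an arm mean undetermined over 3 × 160/34 = 14.1 points, as wide as the planned effect.

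**The case against.** The case against limits the point but does not remove it.

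- **Primary analysis.** Most patients who stop before day 3 fail the 2-day dose condition whether or not QoR40 is taken, so collecting it would change the primary result little. This stands. The exception is a patient who completes two days and stops before 10 AM on day 3.
- **Size.** The non-zero figures assume clearly unequal stopping, all of it among poor recoverers and all before the day-3 assessment. The 20% vs 5% case averages 12.5%, above the planned 10% dropout. Patients and research staff are blinded, which makes a large imbalance less likely. A 3-point bias is about 0.4 of a standard error (30 × √(2/31) = 7.6). All of this stands, and the figures are illustrations only.
- **Other data.** Pain, diet, steps, laboratory values, complications, adverse events and inhalation time are still recorded, so unequal stopping would be visible. This stands too, but none of it supplies the missing QoR40.

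Three stronger readings are tempting, and the documents do not support them. A reader might infer that the insufficient-gas analysis cannot be run at all; it can, for under-dosed patients who did not discontinue. A reader might infer that every discontinuer lacks the primary outcome; those who stop after 10 AM on day 3 have it. A reader might infer that the missing patients are the sickest; the serious-adverse-event rule makes that plausible for some, but patients may stop for other reasons and no early event rate is given.

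**Conclusion.** The point holds in limited form. The collection rule contradicts both the intention-to-treat promise and the complete-data aim in its own paragraph. Nothing else in the article resolves this. With no handling of missing scores, the intention-to-treat t-test excludes everyone who stopped before 10 AM on day 3, and the insufficient-gas test excludes those who are short because they stopped in that window. The loss is likely informative because serious adverse events stop the gas.

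The size cannot be fixed from the documents. It is zero with equal and similar stopping, and roughly 2 to 6 points against 14 under the unequal scenarios shown. Under the rule as written, nobody could establish from QoR40 which of these applied. It should be corrected while recruitment continues, because uncollected scores cannot be recovered.

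**What to change.** In Interventions and data collection, delete the exception for QoR40 and urinary 8-OHdG and the statement that discontinuers are out of the study. State instead that QoR40 (day 3, day 7, discharge) and urinary 8-OHdG are collected at the scheduled times from every randomised patient regardless of gas discontinuation, unless consent to data collection is withdrawn. In Analysis of efficacy, state that the intention-to-treat analysis includes all of them by randomised arm. A likelihood-based repeated-measures model is one option for scores that are still missing; it is not essential to the correction. The clinical rule for stopping the gas is unchanged.

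The cost is a short protocol amendment and a few extra questionnaires and urine samples from patients already followed to discharge. Two limits remain. Enrolment began on 9 March 2021, so scores of any patients who have already discontinued are lost. Some very ill patients may still be unable to complete the form.

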**Fig. 1 Fig1:**
[figure not shown]
From postoperative day 1 to day 7, groups A and B (34 subjects each) will receive 5% hydrogen gas and air, respectively

**Table 1 Tab1:**
[figure not shown]
Study schedule

*QoR40* the 40-item quality of recovery questionnaire

Participant files are to be stored in numerical order in a secure and locked location. Participant files will be maintained in storage for 10 years after completion of the study.

#### Primary endpoint

The postoperative recovery level (QoR40) on postoperative day 3 will be evaluated to examine the effectiveness of the hydrogen gas inhalation treatment. The QoR40 will be measured using a questionnaire on postoperative QOL which will be distributed preoperatively. Each patient will independently fill out the questionnaire himself/herself. The scores will be totaled (perfect score: 200 points), and the resulting number will be evaluated as the patient satisfaction level and recovery level. The questionnaire survey will be conducted at 10 AM on postoperative day 3.

The results of previous reports infer that hydrogen gas inhalation has wide effects on many aspects, such as on inflammation and liver function, by inhibiting ROS. The primary endpoint, therefore, is established as the QoR40 on postoperative day 3. A subinvestigator will record the results of the questionnaire in the case report form after the patient is discharged.

#### Secondary endpoints

Data on the following items will be collected chronologically during the study period and comprehensive and exploratory evaluations will be performed.
QoR40s besides that on postoperative day 3Grade of postoperative complications (Clavien-Dindo score): The attending physician will record it in the medical record at discharge.Level of pain (NRS): The attending physician or attending nurse will record it in the medical record after interviewing the patients.Amount of dietary intake: The amount of dietary intake is assessed at breakfast, lunch, and dinner, and 100% is a completely eaten meal. The attending nurse will visually determine the amount of uneaten food to evaluate the amount of dietary intake and will record it in the medical record.Number of pedometer-assessed steps: The number of steps per day will be measured using a pedometer, and the attending nurse will confirm it and record it in the medical record.Inflammatory response (WBC, CRP, neutrophil count, and lymphocyte count): They will be automatically recorded in the medical record.Liver function (T-BIL, AST, ALT, ALP, albumin, platelet count, PT, and ICG): All measurements will be automatically recorded in the medical record.Reactive oxygen level (urinary 8-OHdG* level): *This level reflects the level of oxidative damage to DNA caused by excessive reactive oxygen species. A subinvestigator will measure it and will record it in the case report form.Adverse events: CTCAE version 5.0.

A subinvestigator will enter the aforementioned medical record data in the case report form after discharge.

### Safety evaluation

No clinical trial has previously reported any side effects of hydrogen gas inhalation. In this trial, however, the administration of study gas will be immediately discontinued if any serious adverse event occurs.

All adverse events will be recorded and serious adverse events will be totaled separately. If adverse events occur after study gas administration, they will be totaled separately for group A and group B. In addition, the number of patients who experienced the adverse event, number of adverse event episodes, and incidence of adverse events will be determined, and a comparison will be made between groups A and B. All adverse events will be examined regardless of the causal relationship.

Descriptive statistics will be used for clinical test results for each of groups A and B, and clinically significant changes will be totaled. For other parameters, descriptive statistical values will be calculated by group according to the variable type (continuous or categorical variable), or frequencies will be totaled.

A Data and Safety Monitoring Committee (DSMC) will be established independently from the investigator and sponsor. The DSMC comprises an academic pharmacologist, hepatologist, and hepatobiliary surgeon, and the members will review the unblinded study data or whenever an adverse event is reported. The DSMC will advise on continuing or stopping the study based on safety and efficacy considerations.

### Statistical analysis

For the primary analysis, an unpaired *t*-test with common variance (PPS analysis) will be performed to compare the mean of the QoR40 on postoperative day 3 between groups. The subject population to be analyzed will consist of patients who will have consented to trial participation; who will have been administered, according to schedule, at least the minimum dose of their respective gas for at least 2 days; and whose QoR40 on postoperative day 3 will have been measured. The daily minimum dose will be converted to the duration of administration (3-h duration per day) and will be administered in at least 6 h to less than 7 h. In the sensitivity analysis, a *t*-test will be used on the per-protocol population and similarly on a population which includes patients who received insufficient gas. Content with a focus on the non-unique content will be noted in a statistical analysis plan. No compensation for missing data will be made. The statistical significance level will be set at 5% (two-sided) with a confidence interval of 95% (two-sided). No interim analysis will be performed.

For other items, the effects of hydrogen inhalation will be examined by parameters, such as the extent of hepatectomy (segmentectomy or more extensive resection vs subsegmentectomy or less extensive resection) and hepatic ischemia time (30 min or more vs less than 30 min). In addition, comprehensive and exploratory examinations will be performed, including a comparison of patients with high QoR40 scores and patient characteristics.

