### Sample size estimation

In the field of this study, the QoR40 is constructed from 40 items related to “physical comfort,” “emotional state,” “physical independence,” “psychological support,” and “pain.” The maximum score per item is 5 points and the perfect total score, therefore, is 200 points [6]. In hemodialysis patients, it has been reported that symptoms of fatigue were reduced by approximately 30% using a dialysate containing dissolved molecular hydrogen [11]. Molecular hydrogen might affect particularly “physical comfort” and “emotional state” among the 20 items of the QoR40. The results will be considered clinically meaningful if hydrogen gas inhalation is to improve the items of “physical comfort” and “emotion state” by approximately 20%. If such improvement in scores occurs, the hydrogen gas inhalation group will be estimated to score approximately 16 points more than the air inhalation group and to have an average of approximately 153 points. When factors are considered, the estimated average of the hydrogen inhalation group will be 151 points, that of the non-hydrogen inhalation group will be 137 points, and the variance of data 30 points (same in both groups). If α-error and power are set at 0.20 and 70%, respectively, for a two-sided test, then 31 subjects per group (total of 62 subjects) will need to be enrolled in this study. If it is estimated that approximately 10% of the subjects will drop out, the target number of subjects will be 68.

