### Randomization and allocation concealment

After the research team obtains patient consent from the recruited participants, web-based registration and minimization method of random allocation will be performed at the data center of Medical Research Support, a company located in Japan that is independent of the research team. Medical Research Support will generate web-based randomization sequences. The research team cannot access the randomization process and will be informed of the results of the randomization via email from Medical Research Support. The minimization method of random allocation prevents the prediction of study allocation. Then, the registration numbers and the allocation results will be added to the eligibility criteria checklist. The information will be faxed to the data center, resulting in patient registration.

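### The primary t-test on day-3 QoR40 leaves out the preoperative QoR40 and the minimisation factors: it is valid, but less precise than the planned data allow

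*Protocol article*

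**What the plan says.** The Statistical analysis section of the protocol article names an unpaired common-variance t-test as the primary analysis; it "will be performed to compare the mean of the QoR40 on postoperative day 3 between groups". The sensitivity analyses in the same section are t-tests too. No section puts a covariate into the primary comparison.

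Two other sections describe information this test does not use:

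- Interventions and data collection, on QoR40: "Subjects will fill out themselves the previously distributed questionnaire preoperatively, on postoperative days 3 and 7, and at discharge".
- Randomization and allocation concealment: "web-based registration and minimization method of random allocation will be performed". The article does not name the factors. The full protocol may, and their absence here is not part of this point.

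The article refers to a statistical analysis plan that is not shown. The primary test itself is already fixed in the article, so a plan that substituted an adjusted model would depart from it.

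**The concern.** A patient's preoperative QoR40 is likely to predict the day-3 score to some degree. A model that includes it removes that part of the between-patient variation from the error term; the t-test leaves it in.

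Minimisation raises a related matter. It makes the arms more alike on its factors than simple randomisation would. If those factors predict the outcome, the estimated difference varies less from trial to trial than the pooled SD implies. The t-test's standard error is then too large and the test rejects less often than its nominal level.

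What is at stake is precision. Under the article's own assumptions the 95% interval reaches further either side of the estimate than the 14-point effect the trial is designed to find, so any gain from data already planned is worth having.

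**Working it through.** **Inputs from the article**

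- Means (Sample size estimation): "the estimated average of the hydrogen inhalation group will be 151 points, that of the non-hydrogen inhalation group will be 137 points", a difference of 14 points.
- Spread (same section): "the variance of data 30 points (same in both groups"). Only an SD of 30 reproduces the stated sample size; a true variance of 30 would need 1 patient per group.
- 31 per group before dropout; planning alpha 0.20 two-sided; power 70%.
- Analysis level 5% two-sided with a 95% interval (Statistical analysis).

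**Assumptions, not in the article**

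- The correlation rho between preoperative and day-3 QoR40.
- The share of outcome variance (R²) that the minimisation factors explain.

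**1. The article's own figure.** For an unadjusted comparison of 14 points with SD 30 at two-sided 0.20, the noncentral t gives 69.7% power at 30 per group and 70.7% at 31. The stated 31 per group reproduces, and it rests on the unadjusted test.

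**2. The unadjusted test at the 5% analysis level.** SE = 30 × √(2/31) = 7.62 points. Noncentrality = 14/7.62 = 1.84 on 60 df. Power = 44.0%. Half-width = 2.00 × 7.62 = 15.2 points.

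**3. Adding preoperative QoR40.** Residual SD = 30 × √(1 − rho²), with 59 df. The formula ignores the small addition to the adjusted SE from chance baseline imbalance.

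| rho (assumed) | Residual SD | SE | 95% CI half-width | Power at 5% |
|---|---|---|---|---|
| unadjusted | 30.0 | 7.62 | 15.2 | 44.0% |
| 0.2 | 29.4 | 7.47 | 14.9 | 45.4% |
| 0.3 | 28.6 | 7.27 | 14.5 | 47.4% |
| 0.5 | 26.0 | 6.60 | 13.2 | 55.1% |
| 0.6 | 24.0 | 6.10 | 12.2 | 61.8% |

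At rho = 0 the only loss is one degree of freedom: power goes from 43.96% to 43.94%. At the planning alpha of 0.20, power goes from 71% unadjusted to 74%, 80% and 84% at rho 0.3, 0.5 and 0.6.

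**4. Minimisation factors.** With exact balance, the true type I error of the unadjusted test is about 2 × [1 − Φ(1.96/√(1 − R²))]. For R² = 0.2 this is 2 × [1 − Φ(2.19)] = 2.8%. Minimisation does not balance exactly, so it was also simulated: 62 patients, two evenly split binary factors, biased-coin probability 0.8 (all design details assumed), with 8,000 runs for type I error and 4,000 for power.

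| R² (assumed) | Type I error, t-test | Type I error, adjusted | Power, t-test | Power, adjusted |
|---|---|---|---|---|
| 0 | 5.1% | 5.1% | 44.0% | 43.9% |
| 0.2 | 3.1% | 5.2% | 43.1% | 52.4% |
| 0.4 | 1.3% | 4.8% | 42.6% | 65.5% |

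The simulation analyses everyone allocated. The article's primary set is per-protocol, so the balance achieved at allocation may be weaker there.

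**The case against.** The strongest reply is that nothing here is an error. Under randomisation an unadjusted t-test is unbiased and holds its level; under minimisation it errs on the cautious side. It also matches the sample-size calculation. This stands: the point is about efficiency, not validity. A reader might infer that the planned confidence interval is wrong. For preoperative QoR40 it is only wider than it need be. It overstates the uncertainty only if the unnamed minimisation factors are prognostic and remain balanced in the per-protocol set.

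It is also fair to say that the gain is unknown. At rho 0.2 it is about one percentage point of power. Nor does a chance baseline difference between arms escape the t-test, whose standard error already allows for it.

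A reader might also infer a conflict over the endpoint, because Analysis of efficacy states: "The measure of the efficacy of the primary endpoint is the improvement of the QoR40 of the per-protocol population on postoperative day 3". That could suggest change from baseline. The article does not support this reading. The Abstract, Methods/design, Interventions and data collection, Primary endpoint, Statistical analysis and Table 2 all give the endpoint as the day-3 score. Sample size estimation turns its expected improvement into a higher mean in the hydrogen group than in the air group. The wording is loose, but no section proposes a change-score analysis.

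Finally, adjustment has a practical cost. The primary set requires a day-3 score but not a preoperative one, and the article rules out compensating for missing data. A plain ANCOVA would therefore drop anyone without a baseline score. That stands and has to be handled in the fix.

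**Conclusion.** The point holds as a matter of precision. The fixed primary test is valid but leaves out a baseline score that every patient is due to complete, and the factors used in allocation. Under the article's figures (31 per arm, SD 30, 14 points, two-sided 5%), adjusting for preoperative QoR40 would raise power from 44% to between 45% and 62% and shorten the half-width from 15.2 to between 14.9 and 12.2 points, for assumed correlations of 0.2 to 0.6. With no correlation the loss is negligible.

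The minimisation part is conditional: type I error of about 3% if the factors explain 20% of the variance and stay balanced, and no effect if they are not prognostic.

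It would be wrong to conclude that the lack of adjustment is the main reason for the 44%. That comes chiefly from sizing the trial at alpha 0.20 and testing at 5%. At 5%, 70% power needs about 57 per group unadjusted, and still about 37 per group at a correlation of 0.6 (normal approximation). Adjustment helps but does not close that gap.

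**What to change.** - Make the primary analysis an ANCOVA of day-3 QoR40 on treatment, preoperative QoR40 and the minimisation factors. Report the adjusted mean difference with its 95% CI, and keep the unpaired t-test as a supportive analysis.
- State how a missing preoperative score is handled so that no patient is lost for that reason, for example by imputing the mean of the baseline covariate. Word this as an explicit exception to the rule against compensating for missing data.
- Make the change before unblinding, by a dated and documented amendment. The Blinding section gives the statistician and the principal investigator knowledge of the allocation, so the amendment should also precede any comparison of outcomes by arm.

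The cost is one degree of freedom per covariate (the total depends on how many minimisation factors there are) and an amendment while recruitment is open. No further data collection is needed. The mismatch between alpha 0.20 and 5% has to be resolved separately.
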